## 1. Introduction

Current standard treatment for drug susceptible tuberculosis (DS-TB) was designed 40 years ago and has remained unchanged except for a 4-month regimen using high-dose rifapentine and moxifloxacin following the results of a recent clinical trial [1]. Rifampicin is still the backbone drug in the treatment of DS-TB because of its potent bactericidal and sterilizing activity. The currently used once daily 10 mg/kg dosing of rifampicin was selected in the 1970s and was based on pharmacokinetics, toxicity, and cost concerns [2]. Under clinical trial conditions and using per protocol analysis, the current standard regimen achieves a 95% efficacy [3]. However, several pharmacological, bacterial, and host factors may negatively affect treatment outcomes in daily practice.

Some groups of people are more vulnerable to TB because of risk factors (e.g., advanced age, immunosuppression, diabetes, or liver disease) that increase their risk of active disease and poor treatment outcomes [4]. For example, treatment success rate was 86% globally, but only 77% for people living with HIV [5]. Drug-induced liver injury is the best-known adverse reaction associated with rifampicin, isoniazid, and pyrazinamide. In addition, rifampicin typically causes gastrointestinal symptoms and hypersensitivity reactions (pruritus, rash, flu-like syndrome, hemolytic anemia). Although for clinicians these groups are also considered more vulnerable to adverse reactions, different studies show contradictory results. For example, in a retrospective study including 1149 patients, age > 60, diabetes, and hepatitis B virus (HBV) infection were not associated with an increased risk of adverse reactions [6].

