### 2.5. Recruitment

Participants will be prospectively included and compared with historical controls from the same sites. Participants meeting all the inclusion and not any of the exclusion criteria will be offered to start on the HR^35^ZE arm. After 8 weeks, participants will be managed according to the national TB guidelines.

The selected retrospective participants will provide a comparison for the primary safety outcome, and to the secondary efficacy outcome of culture conversion at 8 weeks using MGIT media. 

We adhered to all Pockock’s principles for historical controls except for the use of information from participants that were previously randomized in clinical trials [23]. To avoid the selection bias that may arise because of this limitation, we aim to include all adult patients fulfilling the inclusion criteria treated with HR^10^ZE in the participating sites between January 2017 and December 2019 (to avoid the influence of the 2020–2021 SARS-CoV-2 pandemic in TB diagnoses and follow-up). Thus, the records of all patients from that period with pulmonary and extrapulmonary rifampicin susceptible tuberculosis will be reviewed. We will capture the severe or grade 3 adverse events and week 8 microbiological status from those who are ≥60 years, or ≥18 years and have a diagnosis of diabetes, malnutrition, HIV, HBV or HCV coinfection, other stable chronic liver diseases, or TB meningitis, and have no pharmacological immunosuppression. We intend to control the retrospective cohort to match the prospective one for age, sex, cavitation in lung TB, and severity in TB meningitis. In case not enough matched controls are not found, we will extend the search with patients until the calculated sample size in the control arm is achieved. The historical cohort will include participants from only Spain, Portugal, and Paraguay and not likely from the Netherlands, as optimized doses of rifampicin have been used in both Dutch sites for more than a decade in the same participant subgroups as included in our study.

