### 2.9. Sample Size Assumptions and Justification

For the sample size calculation, a non-inferiority design is assumed and the upper limit of the 95% confidence interval (CI) of the difference of proportions in grade 3 or higher adverse events at 8 percentage points has been set. We assume that 5% of patients will not be assessable. Alpha risk is set in 0.1 and power in 0.8. Based on the previous literature and our previous experience, expected standard treatment grade ≥ 3 AE are 5–10% (mean 8%) among experimental arms and standard treatment arms. Considering this, the number of participants per arm has been calculated to be 134 participants. Because of the limited recruitment capacity for this trial, we could not target specific numbers of participants for each sub-group of risk factors. 

Based on a feasibility survey performed at the planning stage, the target enrollment rates per country were: Paraguay 6.25 participants per month; Spain, Portugal, and the Netherlands 1.6 participants per month.

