## 3. Discussion

RIAlta is a multinational, open label, non-randomized phase 2b/c trial that aims to bridge an important knowledge gap on the safety of optimized rifampicin doses in vulnerable TB patients that are more prone to suboptimal treatment outcomes and drug toxicities because of age and comorbidities. The trial will provide useful information on the efficacy and pharmacokinetics of 35 mg/kg rifampicin dosing and explore possible correlations between occurring adverse events and the rifampicin genetic polymorphisms involved in metabolism and hepatotoxicity. It will evaluate the usefulness of exhaled VOCs as biomarkers of early treatment response. Finally, the study will evaluate the social and economic circumstances of the participants.

There are no validated surrogates for early treatment response for extra-pulmonary TB. Efficacy studies at 8 weeks based on sputum culture conversion does not include this patient population. The cure at the end of treatment is also difficult to confirm in this group because of the need of invasive samples that are not indicated as the procedure might pose extra/unnecessary risks to patients’ lives. As a result, most of the trials exclude persons with extrapulmonary TB and the safety and efficacy information are extrapolated from pulmonary TB studies. It is well known that the pharmacokinetics of antimicrobials may vary according to the site of infection [13]. To address this, our study will obtain information about pulmonary and extrapulmonary TB in parallel. The correlation between intermediate data about sputum culture conversion and change in sputum bacterial load as estimated by the TTP for pulmonary TB participants and change in VOC in all participants will enable us to explore if the breath signature changes could be used as surrogate markers for extra-pulmonary TB. This could open the path for non-invasive biomarker validation and future inclusion of people with extrapulmonary TB in regulatory trials.

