Therefore, the population included in this study belong to the other risk factors groups for failure and relapse that have been under-represented in previous clinical trials [4,22]. As a phase 2 study, the main aim of this clinical trial is to evaluate safety of rifampicin defined as the rate of participants suffering grade 3 or higher adverse events or severely adverse events. This information will be likely available from historical controls although it was not systematically collected. Grade 1–2 adverse events, which are considered tolerability problems, are not typically reported in clinical records, or the information about them is not complete, thus making it difficult to make comparisons. To address this, we have developed adverse events monitoring and management guidelines, which will be harmonized at all centers for the prospective part. Extensive training will be provided to the investigators at each site. 

It is important to acknowledge the main limitations related to this trial design. Because of the limited recruitment capacity within our consortium and budgetary constraints, we decided to use historical controls (rifampicin 10 mg/kg along with the same TB regimen) and assign all prospectively recruited participants to the 35 mg/kg dose. This results in a non-randomized design as all participants will be assigned to the experimental arm and compared with historical controls. Hence, another limitation is that information about tolerability is often incomplete or not reported in clinical records, and the endpoints in the different sub-studies are not performed in daily clinical practice. For similar reasons, the sample size is too small for a formal subgroup analysis. The results will inform a larger phase 3 trial with power calculations for relevant subgroups.

Having one PK sampling at week 4 will allow us to show the percentage of participants reaching the target exposure (AUC/MIC) when in a steady state after rifampicin induction of its own metabolism. In contrast, this approach will not provide information about exposure during the first week of treatment, when most of the bacterial killing occurs. Nevertheless, this knowledge will aid our understanding if optimized rifampicin dosing is more likely to meet target rifampicin exposure. 

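### The matching list omits the qualifying comorbidity and the country, so the primary risk difference is open to confounding that the stated matching does not remove

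*Protocol article*

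**What the plan says.** Section 2.5 (Recruitment) sets out how the historical comparison is built. Prospective participants are "compared with historical controls from the same sites". Controls must fall into the same vulnerable groups as participants, and the sponsor aims to take in all eligible standard-dose patients treated from January 2017 to December 2019. The matching sentence reads: "We intend to control the retrospective cohort to match the prospective one for age, sex, cavitation in lung TB, and severity in TB meningitis". If matched controls run short, "we will extend the search with patients until the calculated sample size in the control arm is achieved".

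The same section later narrows the source: "The historical cohort will include participants from only Spain, Portugal, and Paraguay and not likely from the Netherlands". The reason given is that both Dutch sites have used optimised rifampicin doses in these patient groups for more than a decade. Section 2.3 lists two Dutch centres among the five sites.

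Section 2.9 gives planned accrual as "Paraguay 6.25 participants per month; Spain, Portugal, and the Netherlands 1.6 participants per month" and says that no numbers could be targeted per risk group. The Discussion describes the patients as "more prone to suboptimal treatment outcomes and drug toxicities because of age and comorbidities". On historical safety data it says: "This information will be likely available from historical controls although it was not systematically collected".

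**The concern.** A qualifying condition acts as an entry filter for controls, not as a matching variable. A shared filter does not balance the mix behind it: a participant with chronic liver disease or HIV can be paired with a control who qualified through diabetes or malnutrition alone. By the trial's own premise these conditions bear on toxicity, and the mix in the prospective arm is left to chance.

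Country is not matched either. Historical events were recorded in routine care, so completeness may differ between sites. The primary outcome in section 2.10 also counts non-completion and loss to follow-up, which plausibly vary with the care setting. If participants and controls differ in country mix, such differences enter the risk difference directly.

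At stake is the primary safety conclusion, which turns on an 8-point margin with an expected event rate of about 8%. A shift of a few points either way could change it.

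**Working it through.** **1. The stated sample size, for the scale of the check.** Formula: n = (z for alpha + z for power)² × 2p(1−p) / margin². With p = 0.10 (upper end of the 5–10% in section 2.9), one-sided alpha 0.1, power 0.8 and margin 0.08: (1.2816 + 0.8416)² × 0.18 / 0.0064 = 126.8, so 127 per arm. Then 127/0.95 = 133.7, so 134, the stated figure. At the stated mean of 8% the same formula gives 104, or 110 after dropout. The point here does not depend on this; only the 127 evaluable per arm is carried forward.

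**2. Dutch participants** (rates from section 2.9, assuming accrual follows them). The text does not say whether 1.6 per month applies to each country or to the three together.
- Each: 1.6/(6.25 + 3 × 1.6) = 1.6/11.05 = 14.5%, about 19 of 134.
- Combined, split evenly (assumption): 0.533/7.85 = 6.8%, about 9 of 134.

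**3. Bias from an unmatched factor.** Bias in the risk difference = imbalance in the factor's share × difference in event rate between its levels. The document gives neither input, so both are assumed; entries are percentage points, in either direction.

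| Imbalance | Gap 5 points | Gap 10 | Gap 15 |
|---|---|---|---|
| 10 points | 0.5 | 1.0 | 1.5 |
| 20 points | 1.0 | 2.0 | 3.0 |
| 30 points | 1.5 | 3.0 | 4.5 |
| 40 points | 2.0 | 4.0 | 6.0 |

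A 5-point gap spans the whole of the protocol's 5–10% range; wider gaps go beyond it.

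**4. Country mix: the sign depends on the assumed control mix.** Paraguay supplies 6.25/11.05 = 57% or 6.25/7.85 = 80% of participants. Assume recorded event rates of 4% in Paraguay and 12% elsewhere (both outside the 5–10% range).
- Controls in proportion to the section 2.9 rates without the Netherlands: Paraguay share 6.25/9.45 = 66% or 6.25/7.32 = 85%. Bias = (0.566 − 0.661) × (−0.08) = +0.8 points, or (0.796 − 0.854) × (−0.08) = +0.5 points.
- Controls 40% from Paraguay (no source in the document): (0.566 − 0.40) × (−0.08) = −1.3 points, or (0.796 − 0.40) × (−0.08) = −3.2 points.

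**5. Comorbidity mix (assumed).** Liver disease, viral hepatitis or HIV in 40% of participants and 20% of controls, with rates of 12% against 5%: 0.20 × 0.07 = +1.4 points.

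**6. What a bias would do.** Normal approximation, 127 per arm, control rate 8%, 95% CI bound against 8 points.
- True excess of 8 points: the chance of falsely declaring non-inferiority is 2.5% with no bias, 7.1% at −2 points and 16.6% at −4.
- No true excess: the chance of showing non-inferiority is 65% with no bias, 42% at +2 points and 22% at +4.

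**The case against.** The design has real protections. Controls must meet the same eligibility groups, age (itself a qualifying condition) is matched, and the aim of including all eligible 2017–2019 patients guards against selective choice of controls. These lessen the problem, but none of them balances comorbidity or country.

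The evidence that comorbidity drives toxicity is mixed. The Introduction calls it contradictory and cites a retrospective study of 1149 patients in which age over 60, diabetes and HBV infection "were not associated with an increased risk of adverse reactions". That stands as a reason not to call these factors established drivers. The cited result does not mention HIV, HCV or chronic liver disease, and the Discussion still takes comorbidity as a reason for toxicity.

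That recording differs by country is an inference; the article compares no countries. The Steering Committee reviews severe events in both cohorts (section 2.8), which helps classify recorded events but cannot recover unrecorded ones.

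Sections 2.15 and 3 acknowledge bias from the non-randomised design and present the results as informing future trials rather than changing practice. This is fair, but it is general and does not mention the unmatched factors.

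Three further criticisms might be inferred, and the document does not support them:
- **That no adjustment will be made.** Sections 2.8 and 2.10 mention none, but adjustment is commonly left to a statistical analysis plan or full protocol, neither of which is shown.
- **That cavitation is a misplaced matching variable.** The same controls serve the week-8 culture-conversion comparison, where it is relevant.
- **That the Dutch gap is hidden or certain.** Section 2.5 discloses it, gives the reason and words it as unlikely rather than impossible. What remains is a conflict with that section's opening statement on sites.

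**Conclusion.** The point holds as a gap in the design. The matching list and the source of controls are fixed in this article, and following them can leave the two groups unbalanced on qualifying condition and on country. The primary risk difference is open to confounding from both.

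A reader might go further and conclude that the comparison is confounded, or that it is tilted towards the high dose by as much as 40% of the margin (3.2 of 8 points). The document does not support that. The figure needs an unsourced 40% Paraguay share among controls and event rates outside the protocol's own range. With a control mix built from the protocol's accrual rates, the same event rates give +0.5 to +0.8 points, the opposite sign. The 0.5 to 6 point range is a sensitivity range, not an estimate.

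Firmer is the expectation that about 9 to 19 of 134 participants will lack same-country controls. This rests only on accrual following the planned rates and, for the lower figure, on an even split between three countries.

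**What to change.** In section 2.5, do one of the following:
- add country and qualifying-condition group (liver disease, HBV or HCV; HIV; other) to the matching variables; or
- keep all eligible 2017–2019 controls and weight or standardise them on country, qualifying condition, age and sex.

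Apply the same balance to any control found through the extended search.

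Correct the same-sites statement so that it agrees with the Dutch exception, and report the primary comparison with and without the Dutch participants. Balance on country is not attainable for participants whose country supplies no controls, so state in advance which of the two analyses decides. Leaving the Dutch participants out would reduce the prospective group to about 115 to 125 (134 − 19 or 134 − 9).

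The cost is modest. The qualifying condition must be established anyway to decide whether a control is eligible, and the site is known. Baseline laboratory values such as ALT are not named among the data to be captured, so the fix should not depend on them. The drawback is that close matches become harder to find, with some loss of precision and more reliance on the extended search; weighting all eligible controls limits this.

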### 2.6. Intervention

The intervention in this study is a once daily high-dose of rifampicin at 35 mg/kg. A dose-finding study conducted in South Africa found that 40 mg/kg/day was the maximum tolerated dose in young participants without significant comorbidities [8]. Participants should start anti-TB treatment as soon as possible after signing written informed consent. This protocol allows a window of up to 7 days to complete screening tests (whether TB treatment was initiated or not; see study design diagram: Figure 1). Pyridoxine (vitamin B6) supplementation will be allowed as per local guidelines recommendations. The investigation team will carefully assess other concomitant drugs. When interactions are detected, dose adjustments or substitutions by an alternative drug will be at the discretion of the investigators.

### 2.7. Rifampicin Dosing Strategies

Study participants will receive high dose rifampicin 35 mg/kg for 8 weeks (maximum once daily dose of 3150 mg) by combining fixed-dose combination (FDC) tablets with rifampicin loose capsules (Table 3). We have adapted the WHO guidelines weight band dosing scheme for a more accurate rifampicin dosing. The dose for each band was calculated for the medium weight in each band (45 mg × 35 mg = 1575 mg, rounding 1500 mg), and for those with >80 kg, the dose is calculated for 90 kg (90 mg × 35 mg = 3150 mg).

One limitation is the scarcity of the 600 mg presentation for rifampicin, which would reduce the pill burden for the participants in this trial. For instance, as optimized doses of rifampicin come closer to daily practice, public health decision makers should advocate to increase the availability of rifampicin in high dose presentations to reduce the number of pills taken by patients.

To achieve a similar drug exposure to oral rifampicin at 35 mg/kg/day, the dose for intravenous administration should be 26 mg/kg/day [13].

### 2.8. Assessment of Study Outcomes, Analysis Groups, and Duration of Follow-Up

The primary safety hypothesis is that the incidence of adverse events in the high dose rifampicin (35 mg/kg) supplemented with isoniazid, pyrazinamide, and ethambutol [HR^35^ZE] during the first 8 weeks of treatment will not exceed that of controls on a standard HRZE regimen (rifampicin 10 mg/kg) [HR^10^ZE]. The HR^35^ZE regimen will be considered unsafe if in a non-inferiority analysis, the upper limit of the 95% confidence interval of the difference of proportions in grade ≥ 3 AE (according to CTCAE scale version 5) between the experimental and the historical control arm exceeds 8%. The most common adverse events related to therapy with higher rifampicin doses were vomiting, headache, hyperuricemia, pain in the extremities, and pruritus. No significant differences according to rifampicin dose (from 10 to 35 mg/kg) were found in a recent systematic review and in a retrospective study collecting the real-life experience from a Dutch center [24,25].

To assess the AE and ensure a homogeneous evaluation of their grade, severity, expectedness, and treatment relatedness, we will administer a standardized training for the investigators from all different sites. In addition, both for the prospective and the retrospective cohorts, grade 3 or higher adverse events and SAE will be reviewed by the trial’s Steering Committee for relatedness classification. When no consensus is reached, the Data and Safety Monitoring Board formed by experts independent from the trial will make the final decision.

Tolerability will be measured as any adverse event (grade 1 to 4), treatment dropout rate, and any dose reduction. For efficacy outcome, the hypothesis is that in DS-TB participants (pulmonary disease), the proportion of participants experiencing successful treatment outcomes (culture and smear negative) at the end of the intensive phase of treatment on HR^35^ZE will be non-inferior to that of controls on HR^10^ZE. The HR^35^ZE regimen will be considered ineffective if the lower limit of the 95% CI of the proportion of participants with a negative sputum culture (sputum sterilization), or unable to produce sputum if they have a previous negative culture at week 8, is more than 10% lower than that of historical controls treated with HR^10^ZE. Other exploratory outcomes will be reported descriptively. 

After the trial intervention ends at week 8, participants will be transferred to a standard of care as per national guidelines. We will extend the follow-up duration up to one year after the completion of the treatment to capture relapse-free cures. 

We will use different subsets of the study population for the primary safety, tolerability, and efficacy objectives. Table 2 shows a detailed analysis plan as described in the protocol. 

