### 2.10. Main Outcomes Analysis

The primary safety outcome will be analyzed as the proportion of participants in the HR^35^ZE and historical HR^10^ZE groups that received at least one dose of treatment with an unfavorable outcome after 8 weeks of experimental treatment start. According to the clinical and laboratory information, participants will be classified as having an unfavorable outcome if they suffered one or more grade ≥ 3 AE or SAE that are possibly, probably, or definitely related to rifampicin OR they did not complete their treatment because of other reasons OR were lost-to follow-up. High doses of rifampicin will be considered non-inferior to standard doses if the upper boundary of the 95% CI of the proportion of participants with an unfavorable outcome is less than 8% that of the point estimate in the historical standard dose group.

Efficacy will be assessed as the proportion of participants with pulmonary TB in the HR^35^ZE and the historical HR^10^ZE groups that have sputum culture conversion in liquid media at week 8. The unfavorable efficacy outcome will be defined as having a positive sputum culture at week 8.

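### Section 2.8 turns failure to show non-inferiority into a verdict of 'unsafe' or 'ineffective' and leaves no room for an inconclusive result

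*Protocol article*

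**What the plan says.** Section 2.8 sets two decision rules.

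- **Safety.** The rule opens: "regimen will be considered unsafe if in a non-inferiority analysis, the upper limit of the 95% confidence interval of the difference of proportions". The event is a grade 3 or higher adverse event, HR35ZE is compared with the historical controls, and the threshold for that limit is 8 percentage points.
- **Efficacy.** The rule opens: "regimen will be considered ineffective if the lower limit of the 95% CI of the proportion of participants with a negative sputum culture". It concerns pulmonary disease at week 8, also counts as a success a patient who can no longer give sputum after an earlier negative culture, and puts the threshold 10% below the control result.

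Section 2.10 words the safety conclusion from the other side: "High doses of rifampicin will be considered non-inferior to standard doses if the upper boundary of the 95% CI" clears the 8% criterion. It attaches no conclusion to failure.

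Section 2.9 sizes the trial on the safety endpoint alone and arrives at 134 per arm, including a 5% allowance for unassessable patients. On error rates it says: "Alpha risk is set in 0.1 and power in 0.8". The event rate is taken to be the same in both groups, with a range and a mean: "expected standard treatment grade ≥ 3 AE are 5–10% (mean 8%) among experimental arms and standard treatment arms". The abstract states 80% power and controls in a ratio of 1:1 or higher.

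**The concern.** An upper limit above 8 points means that an excess of 8 points has not been ruled out. It does not mean that an excess has been shown. Section 2.8 treats the two as the same: it sets no condition on the lower limit and has no inconclusive category. The efficacy rule has the same structure.

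The label would then often be driven by imprecision rather than toxicity. The discussion says the results will inform a larger phase 3 trial, so a prespecified verdict of 'unsafe' that the interval does not support would mislead those who use it.

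**Working it through.** **Inputs from the documents.** Margin 8 points and 95% CI of the difference (2.8); 134 per arm, 5% not assessable, expected rate 5-10% with mean 8% in both arms, alpha 0.10, power 0.80 (2.9); controls at least 1:1 (abstract). Evaluable per arm: 134 × 0.95 ≈ 127.

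**Reproducing 134.** With one-sided alpha 0.10 and 10% in both arms:

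n = (1.2816 + 0.8416)² × 2 × 0.10 × 0.90 / 0.08² = 126.8, so 127; 127 / 0.95 = 133.7, so 134.

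The mean rate of 8% with a continuity correction also fits (127.5, inflated to 134.2). At equal rates without continuity correction, one-sided 0.05 and 0.025 do not fit (151 and 191 at 8%; 184 and 233 at 10%). The 80% power therefore matches an 80% two-sided interval, not the 95% interval in the rule.

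**Chance that an equally safe regimen is called unsafe.** With true difference zero and 1:1 controls, SE = √(2p(1−p)/127) and P = 1 − Φ(0.08/SE − 1.96).

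| True rate, both arms | SE (points) | 0.08/SE − 1.96 | P (normal) | P (exact: Wald, Newcombe) |
|---|---|---|---|---|
| 5% | 2.74 | 0.965 | 16.7% | 16.4%, 23.7% |
| 8% | 3.40 | 0.390 | 34.8% | 33.9%, 38.3% |
| 10% | 3.77 | 0.165 | 43.4% | 42.5%, 45.3% |

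With 2:1 controls (127 against 254), SE = √(p(1−p)(1/127 + 1/254)), and the normal figures fall to 7.8%, 22.6% and 31.1%.

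**What those verdicts consist of.** At 8% (exact, Wald), 31.2 of the 33.9 percentage points have a lower limit at or below zero. Only 2.7 have an interval wholly above zero.

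**An example.** 12/127 (9.4%) against 10/127 (7.9%): difference 1.6 points, SE = √(0.0945 × 0.9055/127 + 0.0787 × 0.9213/127) = 3.5 points, 95% CI −5.3 to +8.5. Two extra events would be declared unsafe.

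**Efficacy.** The documents give neither the number with pulmonary TB nor the expected conversion rate, so both are assumed. I read the rule as the CI of the difference: P = 1 − Φ(0.10/√(2p(1−p)/n) − 1.96).

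- n = 60 per arm, 70% conversion: SE 8.37 points, P = 77.8%.
- n = 127 per arm, 95% conversion: SE 2.73 points, P = 4.5%.

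Over 60-127 per arm and 70-95% conversion, the chance that an equally effective regimen is called ineffective runs from about 4% to 78%.

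**Effect of separating the two statements.** At 8% in both arms, about 66% of trials would show non-inferiority, 31% would be inconclusive and 2.7% would show evidence of worse safety. For a truly worse regimen (16% against 8%), SE = √(0.16 × 0.84/127 + 0.08 × 0.92/127) = 4.05 points. The lower limit exceeds zero with probability Φ(0.08/0.0405 − 1.96) ≈ 51% (exact 50-51%), and non-inferiority is declared in about 2.5-3%.

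**The case against.** The label could be read as a burden-of-proof convention for vulnerable patients: a regimen not shown to be safe enough is treated as unsafe. Section 2.10 already has conventional wording, and section 2.15 presents the results as informing trial design rather than changing practice. This softens the consequence. It does not change the stated rule, because 2.10 is silent on failure and 2.8 is not.

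The limits on size stand:

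- A reader might infer that the regimen could be called unsafe while the data favour it. At the planned rates this practically does not happen. The half-width is 6.7 points at 8%, so the upper limit passes 8 only with an observed excess above about 1.3 points (0.6 at 10%). By exact enumeration, an unsafe call with an observed difference below zero has probability under 0.01% at 5% and 8%, and at most 0.11% at 10%.
- A reader might infer a false-verdict rate of one in three or more throughout. The plan's own range does not support that: the rate is lower at 5%, and lower with more controls than 1:1.
- Much of the excess over 20% belongs to the mismatch between alpha 0.10 and the 95% interval. Holding failure at 20% at an 8% rate would take 181 evaluable (191 enrolled) per arm. Rewording does not raise the chance of showing non-inferiority.
- No single efficacy percentage is a property of this plan, and a secondary endpoint without its own sample size is ordinary.

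**Conclusion.** The concern holds as a fault in the decision rule. Section 2.8 equates not showing non-inferiority with harm or lack of effect, and nothing else in the article corrects it. That inference is wrong at any sample size: at a true 80% power, one equally safe regimen in five would still be called unsafe.

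Under the plan's own inputs (127 evaluable per arm, 1:1 controls, equal true rates, 95% CI of the difference) the rate is about 34-38% at 8%, 42-45% at 10% and 16-24% at 5%; with 2:1 controls it is about 23% at 8%. These figures treat the arms as independent samples and ignore matching. The efficacy rule shares the logical fault, but its rate cannot be determined from the documents. A reader might go further and infer that the rule would end development in these groups; the article does not say so.

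**What to change.** In section 2.8:

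1. Replace the verdicts of unsafe and ineffective with 'non-inferiority not shown', and report the estimated difference with its 95% CI.
2. Speak of evidence of worse safety or efficacy only when the whole 95% CI of the difference lies on the unfavourable side of zero. Keep this separate from the margin result, since both can hold at once: 4/127 against 0/127 gives a Wald interval of 0.1 to 6.2 points, which clears the margin and excludes zero.
3. Call a result that misses the margin with a CI including zero inconclusive.
4. State that the sample size was set for safety only, so the 10-point efficacy comparison is not powered.

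The cost is a wording change, best made before results are known; it needs no added patients or data. One downside should be accepted openly: at a true 8-point excess (16% against 8%), about half of trials would report 'non-inferiority not shown' rather than worse safety. Such a regimen would still very rarely be declared non-inferior.
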